#### (1) Effectiveness study

A multivariate regression analysis will be performed in which outcomes of mental health and quality of life will be compared between the Child-Interview intervention group and the control group (adult-only intervention). This will be done at follow-up (assessment B), 6 months after assessment A and a year after the intervention. Covariates will be taken into account.

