Due to scarcity of resources, the importance of economic evaluation studies has been increasingly acknowledged over the last decade. These studies provide information on the impact of child maltreatment on society and the costs of its treatment, which will help identify cost-effective resources. This knowledge contributes to informed decisions on the funding of services and to policy improvements [27,28]. So far, however, economic evidence on child maltreatment is scarce [27,29]. Corso and colleagues performed two literature reviews [27,29] and found that existing studies have focused mainly on cost of illness and do not include loss of quality of life. To our current knowledge, there have been five economic evaluations relating to child maltreatment, i.e. studies in which two or more interventions were analyzed in terms of the costs of effects. Three of these economic evaluations concerned prevention programs for parents [30-32]. The other two studies focused on sexually abused children in secondary care [33,34]. Economic evidence on the impact of child maltreatment and economic evaluations looking at interventions in this field have been scarce, especially in a Dutch context. The societal costs and effects of AMK involvement in the Netherlands have never been studied, even though AMKs have a pivotal function in stopping maltreatment, and thus in reducing its prevalence. Therefore, the primary aim of this study is to examine the effect of the participation of maltreated children aged 6–18 years in the AMK investigation (Child-Interview intervention) on their mental health and quality of life. As a second aim, this study will examine the balance between additional costs and effects of the Child-Interview intervention in comparison with AMK investigations without this intervention (adult-only intervention), from a societal perspective.

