### Sample size and recruitment

Participants from an ongoing prospective study on the mental health and quality of life of maltreated children after a report to an AMK [35] will be contacted to complete assessments A and B (see Figure 1). Parents and children will be asked to give written informed consent for their participation. Five dyads from the sample of this prospective study were excluded because they did not meet age criteria, while for 22 parent–child dyads maltreatment was not verified during the AMK investigation and for 17 dyads the type of maltreatment did not meet inclusion criteria of the quasi-experiment. Hence, the study sample for the present quasi-experiment will include 117 parent–child dyads. A sample size calculation confirmed that this is a sufficient number of participants. Based on the ability to detect a medium effect size or larger clinical effect (Cohen’s d > 0.45) [37] and tested at a conventional power of (1-beta) 0.80 and alpha of 0.05 (one-tailed testing), a total number of 110 parent–child dyads is required.

Supported by AMK records, this sample will be split up into two groups: an intervention group, in which the Child-Interview intervention was used during the AMK investigation, and a control group, in which the intervention was not used (adult-only intervention).

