### Outcome measures

#### (1) Effectiveness study

##### Mental health

Children’s mental health (in terms of internalizing and externalizing psychological problems) as observed by the parents, will be measured with the Dutch version of the Child Behavior Checklist (CBCL) [38]. Parents will be asked to what extent they observe various behavioral and emotional problems in their child. The CBCL uses a 3-point scale and consists of 113 items. Internal consistency is good (α .97) [38].

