## Discussion

The value of having children participate in the AMK investigations by using the Child-Interview intervention is increasingly being recognized. The intervention yields valuable information to substantiate the alleged maltreatment report, and the intervention is also expected to be beneficial for the mental health and quality of life of the maltreated children. However, this beneficial effect has not yet been studied. In addition, child maltreatment is associated with substantial societal costs because of the high demand for healthcare and other services by both the maltreated children and their families. Using the Child-Interview intervention may prevent or reduce negative outcomes of child maltreatment, which may result in a lower consumption of healthcare and other services.

Although the AMK manual suggests that using the Child-Interview intervention during AMK investigation is the preferred method, the AMKs in the Netherlands are still in a transition period as regards the nature of the investigation. From a small survey among AMKs we estimate that the adult-only intervention is still used in approximately 40% of all investigations by the AMKs. At this point in time, this enables us to answer the research questions by means of the proposed quasi-experimental design, before the Child-Interview intervention is fully adopted, as the percentage of cases in which the intervention is not used is still sufficient. We will be able to derive two study groups with acceptable sample sizes from an ongoing study examining the mental health and quality of life of children reported as being maltreated.

A strong point of the proposed study is the use of child self-reports to collect data on quality of life, one of the main outcome measures of the effectiveness study. Data on quality of life are often collected using proxies, but research findings show discrepancies between child and proxy reports [43]. As a consequence, the value of obtaining children’s self-reports is increasingly recognized and several studies have established the accuracy and reliability of child reports [39,43-45].

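### Two main outcomes share the primary aim, but the stated alpha, power and effect size are tied to neither and no success rule is given; no reading of the article delivers both 5% error and 80% power

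*Protocol article*

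**What the plan says.** The Abstract and the Background state one primary aim, the effect of the "Child-Interview intervention) on their mental health and quality of life".

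Outcome measures gives these two domains different instruments and informants. The first is "Children’s mental health (in terms of internalizing and externalizing psychological problems) as observed by the parents", on the CBCL. The second is the child's own report on the PedsQL, with one overall score. The Discussion refers to "data on quality of life, one of the main outcome measures of the effectiveness study", so quality of life is not secondary.

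Under Analyses, (1) Effectiveness study, a multivariate regression is planned in which "outcomes of mental health and quality of life will be compared between the Child-Interview intervention group and the control group (adult-only intervention", at assessment B, with covariates.

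Sample size and recruitment sets d above 0.45, "tested at a conventional power of (1-beta) 0.80 and alpha of 0.05 (one-tailed testing". It requires 110 dyads and has 117. No outcome is named there.

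The closing paragraph of the Discussion ties the expected benefit to better results on mental health *and* quality of life. It is not worded as a decision rule.

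**The concern.** An alpha, a power and a sample size describe one decision. Here they are printed once, while two outcomes, or three scores if internalizing and externalizing problems are analysed separately, stand under the primary aim. The article does not say whether success means any one result, both results or one joint test, and the stated figures mean something different under each.

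The study is meant to inform policy on the optimal way to investigate reports. If one outcome favours the Child-Interview intervention and the other does not, the study counts as positive under one rule and negative under another. Without a rule, that choice would be made after the results are known.

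**Working it through.** **Inputs.** From Sample size and recruitment: alpha 0.05 one-tailed, power 0.80, d = 0.45, 110 dyads required, 117 available. From the Discussion: the adult-only approach is used in about 40% of investigations. If that carries over to the sample, 0.40 × 117 = 46.8, so the split is about 70:47. The correlation r between outcomes is not given. I assume 0 to 0.8 for error rates and 0.3 to 0.7 for power.

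**1. The plan's own figure.** n per group = 2(1.645 + 0.842)²/0.45² = 61.1, so 62 per group and 124 in total. The stated 110 is not reproduced; it corresponds to d of about 0.475. That is a separate matter, but it means that even one test falls short of 80%.

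**2. One test, 70:47.** Noncentrality = 0.45/√(1/70 + 1/47) = 2.386 on 115 df. Power is 0.766, about 77% (0.771 in the normal approximation used below).

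**3. Any one result counts.** Error = 1 − P(all k statistics ≤ 1.645) under the null. For r = 0 this is 1 − 0.95² = 9.75% for two scores and 1 − 0.95³ = 14.3% for three.

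| r | 2 scores | 3 scores |
|---|---|---|
| 0 | 9.8% | 14.3% |
| 0.3 | 9.3% | 13.0% |
| 0.5 | 8.8% | 11.8% |
| 0.8 | 7.5% | 9.3% |

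Two-sided tests at 0.05 give nearly the same (7.8-9.7% and 9.8-14.3%).

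**4. Both must succeed.** The error is at most 5%. When neither outcome has an effect, it is 2 × 0.05 − 0.088 = 1.2% at r = 0.5. Power with d = 0.45 on both outcomes is 2 × 0.771 − P(at least one significant):

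| r | At least one | Both | Exactly one |
|---|---|---|---|
| 0.3 | 92% | 62% | 29% |
| 0.5 | 89% | 65% | 25% |
| 0.7 | 87% | 68% | 19% |

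The shortfall is not only due to step 1. With exactly 80% per test and independent outcomes, the power for both would be 0.80² = 64%.

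**5. One joint test.** I take Hotelling's T² with 2 and 114 df and noncentrality 2 × 2.386²/(1 + r), which is 8.76, 7.59 and 6.70 at r = 0.3, 0.5 and 0.7. The error is 5% and power is 75%, 68% and 62%. Power would be 86% at r = 0. This test has no direction, and it does not say which outcome improved.

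**6. Split results.** From step 4, exactly one of two outcomes is significant in 19-29% of studies when both effects are 0.45. At d = 0.30 on both it is 25-40%.

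**The case against.** A reader might infer that the false-positive rate is 9-12% instead of 5%. The article does not support that as a statement of fact. The figure needs separate tests, a rule that any one success counts, and a correlation near 0.5, and none of these is stated. The only conclusion wording joins the two outcomes with *and*, and a multivariate regression may mean a joint test. Either reading holds the error at or below 5%. This objection stands, so the error figure can only be given as a conditional range.

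A reader might also infer that a split result is likely. Under the planned effect it is about one in four. The child-proxy discrepancies cited in the Discussion concern quality-of-life data, not parent CBCL against child PedsQL, so they do not raise that figure.

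It can further be said that the testing order and the choice of CBCL score belong in a full protocol or analysis plan that is not shown. That is fair for those details taken alone, and the three-score figures rest on a brief description of the CBCL. It does not dispose of the point, because the article itself commits to an alpha, a sidedness, a power and a sample size for the study. These do not fit its two main outcomes under any of the three rules. The two readings that protect the error rate move the problem to power. The joint test also sits badly with one-tailed testing, although that phrase occurs only in the sample size section.

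**Conclusion.** The point holds in conditional form. The error from chance alone is about 7.5-10% for two scores and 9-14% for three if any one result counts. It is at most 5% if both must succeed or one joint test is used, but power is then about 62-68% or 62-75%. Within these assumptions no reading gives both the stated 5% and the stated 80%.

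The power figures assume 117 dyads split 70:47, no loss to follow-up, d = 0.45 on both outcomes and a correlation of 0.3 to 0.7. With nearly uncorrelated outcomes a joint test could exceed 80%, though it would still not be one-tailed. All rates describe chance only. They say nothing about the selection bias that the article acknowledges for this non-randomized comparison, so they should not be read as the total chance of a wrong claim of effectiveness.

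**What to change.** Before analysis, state one of the following in Sample size and recruitment and in Analyses, (1) Effectiveness study:

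- **Holm** across one prespecified CBCL score and the PedsQL overall score. The smaller p-value is tested at 0.025 and, if significant, the other at 0.05. Both remain main outcomes.
- **A fixed order.** The investigators name one of the two scores at assessment B as primary and tie alpha and d = 0.45 to it. The other is tested at the same alpha only if the first is significant.

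In either case the article should say which CBCL score is meant. It describes mental health through internalizing and externalizing problems and does not define a total score. The remaining subscales are exploratory, with estimates and confidence intervals.

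The cost is a few sentences, with no new data. With Holm, the chance of at least one significant result falls from about 89% to 82% (r = 0.5, d = 0.45 on both). With a fixed order, the second outcome cannot be confirmed if the first fails, and the first test has about 77% power, below the stated 80%.

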#### (2) Economic evaluation study

In this study, additional costs and additional outcomes of the Child-Interview intervention will be compared with those of the adult-only intervention. The incremental cost-effectiveness ratio (ICER) will be expressed as the incremental costs per degree of improvement in mental health of the Child-Interview intervention group in comparison with the control group (adult-only intervention). The incremental cost-utility ratio (ICUR) will be expressed as the incremental costs per QALY of the Child-Interview intervention group in comparison with the control group (adult-only intervention).

The ICER (and ICUR) will be calculated using ICER = (Ci-Cc)/(Ei-Ec), where Ci is the annual total costs of the Child-Interview intervention, Cc the annual costs of the adults-only intervention, Ei the effect at 6-months follow-up for the Child-Interview intervention and Ec the effect at 6-months follow-up of the adult-only intervention. The robustness of the ICER will be checked by non-parametric bootstrapping (1000 times). The bootstrap replications will be used to calculate 95% confidence intervals around the costs. The bootstrapped ratios (ICER and ICUR) will be graphically presented in two ways: (1) plotted in a cost-effectiveness plane, in which the vertical line reflects the difference in costs and the horizontal line reflects the difference in effects, and (2) in a cost-effectiveness acceptability curve, showing the probability that the Child-Interview intervention is cost-effective based on a range of ceiling ratios (the maximum amount of money society is willing to pay to gain one extra unit of effect or a gain in QALY). Additionally, the robustness of the base-case findings will be assessed using a sensitivity analysis [42]. This economic evaluation will be performed from a societal perspective. Bootstrapping will be carried out in Excel.

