### Child-interview intervention vs. adult-only intervention in AMK investigation

All reports to an AMK are discussed in a multidisciplinary team meeting which draws up a plan for the investigation. It is at this team meeting that the choice of AMK investigation with or without the Child-Interview intervention is made, based on information from the person who reported the alleged maltreatment.

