Furthermore, not only will this be the first study to examine the effect of AMK involvement, it will also be the first economic evaluation performed in the Netherlands regarding an intervention for maltreated children. Since economic evaluations on child maltreatment have been scarce, it is expected that not all costs of healthcare and other services will be available yet. These costs will need to be valued for this study, so some of the costs will be based on estimates.

Additionally, many aspects of utility measurement in children have not yet been fully developed. There is a lack of health state classification instruments that consider children’s developmental stages, and there is a need to understand the role of proxies in assessing and valuing children’s health [46]. This is why we chose an alternative method, a visual analogue scale. The advantage of the thermometer method that will be used is that it is simple and therefore easily understood by children. However there are also disadvantages to this method, in that it generates values rather than utilities and does not involve an element of choice, nor decision-making under uncertainty, which may result in lower utility estimates.

A methodological concern for the quasi-experimental design of this study is the potential selection bias. All reports that are filed with the AMKs are discussed in a multidisciplinary team in which decisions about the best AMK investigation approach (Child-Interview intervention vs. adult-only intervention) are made. The choice of intervention is based on information collected from the reporter of the suspected child maltreatment. This reporter can be either a professional or non-professional (such as a neighbor), which may affect the quality and reliability of the information on which the multidisciplinary team must base their decision. In addition, AMK investigation using the Child-Interview intervention is the preferred method according to the manual for AMK investigations [13]. When the adult-only intervention is nevertheless chosen, there may be specific reasons for this, such as parents refusing their child’s participation in the AMK investigation, the child having been seen by a therapist or social worker, in which case this professional is approached to prevent additional strain upon the child, and/or language barriers. As a result of these limitations, the two groups may not be comparable at baseline, causing a concern regarding internal validity.

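### The ICER and ICUR are specified as plain ratios of group differences with a plain bootstrap and no confounder adjustment, although the groups are nonequivalent and the effectiveness analysis does adjust

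*Protocol article*

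**What the plan says.** All references are to the protocol article.

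- **Analyses, (2) Economic evaluation study.** The estimator is given as "The ICER (and ICUR) will be calculated using ICER = (Ci-Cc)/(Ei-Ec". The cost terms are defined as follows: "where Ci is the annual total costs of the Child-Interview intervention, Cc the annual costs of the adults-only intervention". The effect terms follow the same pattern: "Ei the effect at 6-months follow-up for the Child-Interview intervention", and likewise for the adult-only group. Uncertainty is handled by resampling: "The robustness of the ICER will be checked by non-parametric bootstrapping (1000 times". The software is fixed too: "Bootstrapping will be carried out in Excel". The replicates feed the confidence intervals for costs, the cost-effectiveness plane and the acceptability curve. A sensitivity analysis is announced without content.
- **Analyses, (1) Effectiveness study.** Here, and only here, the article says: "Covariates will be taken into account".
- **Analyses, opening paragraph.** Baseline characteristics, including costs and outcomes, are to be compared between the groups by tests. Nothing is said about what follows from an imbalance.
- **Child-interview intervention vs. adult-only intervention in AMK investigation.** The multidisciplinary team chooses the approach, "based on information from the person who reported the alleged maltreatment".
- **Discussion.** The authors concede that "the two groups may not be comparable at baseline, causing a concern regarding internal validity". They list possible reasons for the adult-only approach: parental refusal, a professional already seeing the child, and language barriers.

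**The concern.** A ratio of group differences with a simple bootstrap suits randomised groups, where the expected difference at the start is zero. Here the article itself calls the groups nonequivalent, and at least one possible reason for being in the control group bears directly on the cost outcome. Existing contact with a therapist or social worker can lead to the adult-only approach, and both kinds of service are on the list of costed items under Outcome measures, Societal costs.

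The second aim, the balance of extra costs and effects, would then rest on a possibly confounded difference. The acceptability curve would turn that difference into a probability of being cost-effective that takes no account of confounding. The study could also report two different mental-health effects for the same comparison: a covariate-adjusted one for effectiveness, and one with no stated adjustment in the denominator of the ICER.

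**Working it through.** The article gives no cost, effect or imbalance figures, so there is no figure of its own to reproduce and no trial-specific ICER can be computed. The check has two parts.

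**1. The two analyses side by side**

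| Element | Effectiveness study | Economic evaluation |
|---|---|---|
| Estimator | Multivariate regression | Ratio of group differences |
| Covariates | Taken into account, not named | None mentioned |
| Uncertainty | From the model | Non-parametric bootstrap, 1000 replicates, Excel |
| Use of the baseline comparison | Not stated | Not stated |

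The economic section fixes the formula, the number of replicates and the software. It describes no regression, weighting or matching step.

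**2. What an unadjusted difference would estimate**

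For a confounder with a given imbalance between the groups:

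expected raw difference = true difference + (imbalance × slope of the outcome on the confounder)

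Resampling the same dyads reproduces the sampling error around this sum. It does not remove the second term.

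*From the article:* 117 dyads, with the adult-only approach used in about 40% of investigations. 0.60 × 117 = 70.2 and 0.40 × 117 = 46.8, so about 70 and 47.

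*Assumed, with no source in the article:* one confounder; imbalance 0.2 to 0.6 SD; correlation 0.3 to 0.5 with both cost and effect; signs chosen so that the bias favours the Child-Interview; true differences in cost and effect both zero.

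*Bias by the formula:* smallest 0.2 × 0.3 = 0.06 SD; largest 0.6 × 0.5 = 0.30 SD.

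*Simulation, 2000 runs per setting:*

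| Imbalance (SD) | Correlation | Raw effect difference | Raw cost difference | Better and cheaper: raw / adjusted | Net benefit > 0: raw / adjusted |
|---|---|---|---|---|---|
| 0.2 | 0.3 | 0.063 | −0.055 | 40% / 25% | 68% / 50% |
| 0.4 | 0.3 | 0.131 | −0.115 | 57% / 25% | 81% / 50% |
| 0.4 | 0.5 | 0.198 | −0.205 | 75% / 26% | 91% / 51% |
| 0.6 | 0.5 | 0.297 | −0.293 | 89% / 24% | 98% / 48% |

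Net benefit here values 1 SD of effect at 1 SD of cost. With no true difference, the correct shares are about 25% and 50%.

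*Hand check of the extreme rows.* The expected raw net benefit is 2 × correlation × imbalance. Its standard error is √[(2 + 2 × correlation²)(1/70 + 1/47)], with 1/70 + 1/47 = 0.03556.

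- Smallest: 0.12 / √(2.18 × 0.03556) = 0.12 / 0.278 = 0.43, a probability of about 67%.
- Largest: 0.60 / √(2.5 × 0.03556) = 0.60 / 0.298 = 2.01, a probability of about 98%.

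Both agree with the simulation. If the sign of the imbalance is reversed, symmetry turns 68% to 98% into about 32% to 2%. The mechanism is certain, but its direction in this study is not.

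**The case against.** The strongest defence is that the article never calls the four terms raw or unadjusted. The ratio is the generic definition of an ICER. Adjusted costs and effects could be put into it, and a non-parametric bootstrap is compatible with refitting a model in every replicate. A condensed article may leave such detail to a fuller plan. The authors also compare baseline costs and outcomes, announce a sensitivity analysis and openly admit possible selection bias.

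Part of this stands: the absence of adjustment is read from the formula and from what is missing around it. But the section goes well beyond a bare definition, and the neighbouring section does mention covariates. A test of baseline similarity with no stated consequence does not correct the base case, nor does a sensitivity analysis of unknown content.

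Four stronger readings are tempting and are not supported:

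- *That families select themselves.* The AMK team decides; parental refusal is only one possible reason.
- *That all the selection bias passes through.* QALYs are built from the change in utility between assessments A and B, and the ICER is phrased in terms of improvement, so part of a stable difference may drop out. Costs are not change scores, however, and assessment A takes place 6 months after the investigation, so it is no true baseline.
- *That the Child-Interview will look cheaper.* Prior care could raise control-group costs, but refusal or language barriers could go with lower service use. The requirement of sufficient verbal capacity may also limit the language difference.
- *That assessment 1 scores are a ready remedy.* The note to Figure 1 says assessment 1 has no connection with the quasi-experiment, and dyads were recruited during the investigation. The article does not show that these scores are available or precede the interview.

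**Conclusion.** The point holds as a defect in the stated economic method. As written, the ICER and ICUR have no confounder control in groups that the article calls nonequivalent, and they are out of step with the effectiveness analysis. Every output derived from the bootstrap would show sampling uncertainty only.

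The size and direction of any bias cannot be determined from the article. The 0.06 to 0.30 SD range and the shares in the tables depend wholly on the assumed imbalances, correlations and signs. They show that moderate imbalance can matter, not that it will occur here. The conclusion also assumes that the formula is applied to the groups' own costs and effects, which is the natural reading but is not stated outright.

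**What to change.** In the Analyses section on the economic evaluation:

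1. State that incremental costs and incremental effects are estimated with adjustment, by regression (for example seemingly unrelated regressions for cost and effect) or by propensity weighting.
2. Use a short set of pre-investigation covariates, fixed in advance and identical to the set in the effectiveness analysis. Candidates are age, type of maltreatment and, where AMK records hold them, type of reporter, prior professional care and language barrier.
3. Refit the model in every bootstrap replicate, and build the plane and the acceptability curve from the adjusted replicates.
4. Use assessment 1 scores only if they are available and precede the interview. Do not treat assessment A values as baseline, because they may already carry part of the effect.
5. State that residual confounding by unmeasured factors remains.

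The cost is a change of wording, extraction of a few items from AMK records that already serve to form the groups, and a statistics package in place of Excel. No new assessments are needed. Some precision is lost with 117 dyads, which is why the covariate set should be short, and only measured confounding is removed.
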